### Urine and stool sample collection

A urine (required for participation) and stool (if possible) sample will be collected from the participant on day 1 (day of recruitment) and at day 14 and analysed in the research laboratories for presence of bacteria and any resistance profiles. Patients who do not wish to provide stool samples but are happy to participate in all other aspects of the trial will be eligible for recruitment, as the stool samples are not necessary for answering the primary aim of the trial.

Participants will be provided with written instructions on how to collect the urine and stool samples. Urine samples will be collected using a mid-stream urine collection kit (Peezy MSU collection kit) to ensure a clean catch. Stool samples will be collected using an ‘Easy sampler’ kit. Participants will be asked to return samples to the laboratory within 24 hours of collection.

If the clinician requires a urine sample to be sent as part of their clinical management, and there is insufficient urine for both clinical and research samples, the clinical sample will take priority.

Urine samples, from both trial arms, will be transferred to a container containing boric acid for transport to the research laboratory, to arrive at the laboratory within 24 hours for identification and testing of antimicrobial resistance. Results from the research microbiology laboratories will not routinely be disclosed to participating clinicians or patients in either trial arm, but will be available upon request in case of clinical deterioration.

### Data collection

#### Baseline case report form (CRF) – all participants

##### Eligibility

An eligibility CRF will be completed for all consented participants to ensure that they meet the eligibility criteria set out in the protocol. The clinician will then sign the form to confirm eligibility.

##### Randomisation

The randomisation and allocation of eligible participants will be undertaken as part of the data collection process. Whilst completing the baseline CRF, clinicians will be asked to randomise the patient using a password protected POETIC randomisation website. Each practice will be allocated unique login details to the website. The clinician will enter the relevant data into the website, including the required stratifying and balancing variables, which include centre and practice details, and number of presenting symptoms (dysuria, frequency, urgency). The patient must present with at least one of these in order to be eligible for the trial. Once all relevant data has been entered, the randomisation programme will provide the trial allocation for that participant (either Standard care or POCT arm). This information will be recorded on the baseline CRF.

There is no credible blinding mechanism that can be utilised in this trial. Immediately after receiving the allocation, the clinician will need to be aware of the result of the randomisation so as to know whether to use the point of care test or not, and the participant will be need to made aware as they may need to receive a new prescription 24 hours after initial diagnosis, once the POCT results are made available to the clinician.

#### Clinical examination

Following randomisation, participating clinicians will be asked to record details of the patient’s presenting clinical features (signs and symptoms) using a scale of 0-6 for each feature. This CRF also asks the clinician to record: the use of any diagnostic tests (i.e. urine dipstick testing), their antibiotic management for the suspected UTI (including name, dose, and duration of any medication prescribed), as well as any other medication which is either prescribed or advised. The CRF also records if any follow up appointments have been made and if the patient has taken any time off paid employment due to their symptoms.

#### POCT (flexicult) test result CRF – POCT arm participants only

For patients randomised to the POCT strategy, the result of the test should be available 24 hours after inoculation with a urine sample at the baseline consultation. The results of the test and management decisions based on results of the test will be recorded. The time of inoculation will be recorded to ensure that the test is read within 24 hours. The bacterial growth (i.e. no growth, pure growth of an organism or mixed growth, and if mixed growth then presence of predominant growth) will be recorded. The clinician will record number of colonies, the colour of colonies for bacterial identification and the antibiotic resistance of the pure or predominant. The antibiotic resistance will only be completed if the growth is ≥10^3^ cfu/mL. The clinician will then record their management decision after reading the test. This will include if they have prescribed any new antibiotic (including name, dose, and duration). The used POCT will also be photographed using standardised techniques.

### Patient follow-up

#### Symptom diary

Participants in both trial arms will be followed up on the course of their illness and their quality of life, using a two week self-completed daily symptom diary. Participants will be asked on the day that they see their GP to complete questions regarding prior UTIs and whether they had tried to use any products for their symptoms before going to see their GP. Participants will be asked to complete The Patient Enablement Instrument which rates how they are able to cope with and understand their illness [9,10]. On each of the 14 days since seeing their GP, participants will be asked to rate the presence and severity of each symptom using a scale of 0 (No problem) to 6 (Could not be worse) and will also be asked to record any antibiotic use over the 14 days. On day 14, participants are asked to complete a section of the diary which asks if they have seen any healthcare professionals regarding their UTI in the 14 days after seeing their GP.

Participants who do not return their diary will be telephoned by the trial team in order to provide a reminder and enquire whether they need any assistance in returning their diary (new postage-paid envelope for example) or given the option of giving the information required over the phone (minimum data set).

#### Resource use

Resources used in training professionals will be recorded. For POCT patients, all staff time taken to perform the test and to contact the patient to report results will be monitored. For all participants, resource use associated with UTI, including use of antibiotics, non-prescription medicines, hospitalisations, accident and emergency visits, contacts with specialist and time off work will be recorded.

#### Three-month notes review

The primary care medical records for all participants will be examined for the three months following recruitment. Data will be recorded onto paper CRFs and entered onto the online research database. Data collected will include consultations with both primary and secondary care professionals, recurrence of UTI in the three month period following recruitment and whether any antibiotics were prescribed. The results of any urine samples sent for routine laboratory culture will also be recorded.

#### Processing of samples by microbiology laboratories

Urine and stool samples obtained from all patients are analysed in the research laboratories for presence, quantity and identification of significant Gram-negative bacteria and antibiotic susceptibility profiles. All laboratories will be provided with a microbiology manual and standard operating procedures. Data will be recorded onto a standardised spreadsheet provided to each laboratory.

#### Urine processing

In all sites, urine samples from patients in both trial arms will be sent to a pre-identified research microbiology laboratory. Urines will be processed according to the POETIC microbiology manual provided and local standard operating procedures, where necessary.

Urine microscopy will be performed using standard local procedures. Culture will be performed on neat and diluted urine (10^-3^, 10^-6^) spiral-plated onto Columbia blood agar (CBA) (for total colony counts) and UTI Chromogenic agar (for species specific counts). Enumeration of bacteria will be performed 18-24 hours following incubation at 35-37°C. Bacterial counts will be summarised into purity of growth (pure, predominant, mixed 2 organisms & >2 mixed organisms).

Pure or predominant organisms from positive urines will be identified initially with chromogenic agar and confirmed using MALDI-ToF or other suitable laboratory methods.

For all UTI positive samples, organisms present at ≥10^3^ CFU/mL will be stored on cryogenic beads at -80°C. For all samples a sweep of any growth on the CBA plate will be stored on cryogenic beads at -80°C.

Susceptibility testing of positive isolate will be performed following regional research laboratory procedures, in addition, all positive isolates will also sent to the UK research laboratory for additional testing.

#### Stool processing

Stool samples will either be tested on the day of arrival at the laboratory or batched in the fridge until processed.

Dilutions of the stool sample (10^-3^ and 10^-6^) will be spiral plated onto the following antimicrobial screening plates: CBA, UTI Chromogenic agar, CRE media, ESBL media and agar supplemented with the antibiotics ciprofloxacin and gentamycin. Plates will be incubated aerobically for 18-24 hrs at 35 ± 1°C. Only the 3 most predominant species will be counted. Predominant gram negative organisms will be identified using basic microbiology or MALDI-ToF if available.

Isolates will be stored on cryogenic beads at -80°C. For all samples a sweep of any growth on the CBA plate will be stored on cryogenic beads at -80°C.

Susceptibility testing of positive isolate will be performed following regional research laboratory procedures in addition all isolates will also sent to the UK research laboratory for additional MIC testing.

### Analysis

#### Sample size calculation

A total of 614 participants (approximately 154 per network; 307 per arm) are required. We aim to improve appropriate antibiotic prescribing by at least 20% from an expected level of 55%. However, our sample size calculation is based on detecting a difference of 15 percentage points difference from control (i.e. from 55% to 70%). We need a total sample of 460 (230 for each arm) patients for final analysis (significance level α = 0.05, statistical power (1-β) = 0.90) and will recruit 614 patients to allow for a 25% loss to follow up (which requires a first urine and also follow-up via diary or telephone interview).

#### Statistical analysis

The primary outcome will be appropriate antibiotic use on day 3 (with day 1 being the day that the patient consulted with their primary care clinician). For women who are shown to have a UTI, appropriate antibiotic use on day 3 will be defined as use of an antibiotic for which the isolated pathogen has been shown to have in vitro sensitivity (based on laboratory analysis). For women who do not have a UTI, appropriate antibiotic use on day 3 will be defined as no antibiotic use on this day.

The analysis of this primary outcome will be intention-to-treat and will be undertaken utilising a multi-level logistic regression. Whilst this is an individually randomised controlled trial we will use multi-level modelling with patient as the 1^st^ level and practice as the 2^nd^ level, plus we will test for clustering at the clinician level as the outcome could be seen as a clinician behavioural measure. Country will be used as a fixed level covariate at the practice level.

Secondary outcomes will be analysed using multi-level logistic or linear regression as appropriate, except for symptoms/recovery (daily symptom score), which will be modelled over time to allow for the correlation structure between scores on different days.

This trial is not powered for any sub-group analysis, and no interim analysis is planned. Some exploratory sub-group analysis will be done by country, number of symptoms and recent antibiotic history, using the relevant variables to form an interaction term with arm in the model.

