The POETIC trial is an evaluation of a Point of Care Test (POCT) guided UTI management strategy for use in adult women presenting in primary care with suspected uncomplicated UTI. The POCT that will be evaluated is called Flexicult™ and is a simple point of care culture procedure, and provides clinicians, at the point of care, within 24 hours, with a microbiological diagnosis of bacterial UTI by quantifying bacteria in the urine sample (or not) and determining sensitivities of any identified pathogen to the antibiotics most commonly used for UTI in primary care [8].

POETIC aims to determine the clinical effects and costs of this optimised POCT guided diagnostic and treatment strategy for symptoms of uncomplicated UTI on the overall appropriateness of antibiotic prescribing when compared to a “practice based on best available local guidelines” strategy. The POETIC trial will determine whether or not the POCT aids clinicians to more appropriately prescribe antibiotics for uncomplicated UTI’s i.e. minimise the use of antibiotics for women where no bacterial infection is identified, and ensure the narrowest spectrum antibiotic appropriate to the sensitivity of the infecting organisms is prescribed when a bacterial infection is identified, and whether or not the strategy is cost effective.

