**Table 1 Tab1:** **Antibiotics included in Flexicult™ plate for each region**

**UK**	**Netherlands**	**Spain**
Trimethoprim	Trimethoprim	Fosfomycin
Nitrofurantoin	Nitrofurantoin	Nitrofurantoin
Amoxicillin/clavulanate	Amoxicillin/clavulanate	Amoxicillin/clavulanate
Ciprofloxacin	Ciprofloxacin	Ciprofloxacin
Cephalexin	Amoxicillin	Cefuroxime

Clinicians will be provided with training in the management of UTI using the Flexicult™ approach. Two treatment approaches will be available to participating clinicians for patients randomised to this arm:Provide patients with advice about symptomatic management of their UTI for approximately 24 hours and arrange a mechanism for contacting the patient in approximately 24 hours in order to arrange provision of a prescription for antibiotics, or not, as appropriate, based on the results of the Flexicult™ POCT test.Provide patients with a prescription for antibiotics to start immediately and arrange a mechanism for contacting the patient approximately 24 hours later in order to advise the patient to continue taking the antibiotics, stop taking the antibiotics, or switch to an alternative antibiotic, as appropriate, based on the results of the Flexicult test.

Clinicians will be encouraged to adopt the first approach for patients with milder symptoms and/or for those that would be happy/would prefer to wait 24 hours for a more definitive diagnosis, and the latter approach for those with more severe symptoms or who are not happy to delay initiation of antibiotics.

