### Primary objective

The primary outcome will be appropriate antibiotic use on day 3 (with day 1 being the day that the patient consulted with their primary care clinician). For women who are shown to have a UTI. Appropriate antibiotic use on day 3 will be defined as use of an antibiotic for which the isolated pathogen has been shown to have *in vitro* sensitivity (based on laboratory analysis). For women who do not have a UTI, appropriate antibiotic use on day 3 will be defined as no antibiotic use on this day. In the UK the definition of a UTI is defined for the POETIC trial as ≥10^5^ colony forming units per millilitre (cfu/ml) of a pure/predominant recognised uropathogen, however the varying definitions across the countries will be considered.

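### The day-3 scoring rule counts any antibiotic course finished on day 1 or 2 as no use, so completed short courses are misclassified in women with and without UTI

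*Protocol article*

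**What the plan says.** The protocol article gives the same two-part rule under Primary objective and under Statistical analysis. For women shown to have a UTI, success is "use of an antibiotic for which the isolated pathogen has been shown to have in vitro sensitivity", judged on day 3. For the others: "For women who do not have a UTI, appropriate antibiotic use on day 3 will be defined as no antibiotic use on this day". The clock is fixed by "with day 1 being the day that the patient consulted with their primary care clinician". Neither section mentions a course completed before day 3.

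The Background gives the aim for uninfected women as to "minimise the use of antibiotics for women where no bacterial infection is identified", with no restriction to one day.

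Trial intervention (text below Table 1) describes two routes in the POCT arm. In one, the clinician advises on symptoms and will "arrange a mechanism for contacting the patient in approximately 24 hours" about a prescription. In the other, the woman starts an antibiotic at once and is told about a day later to continue, "stop taking the antibiotics, or switch to an alternative antibiotic". Under Control arm, management follows national guidelines; the section does not say when antibiotics start. Trial intervention says the plates carry the drugs most commonly used in each region, and Table 1 lists fosfomycin for Spain. No course length is given for any drug.

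**The concern.** The rule treats use on day 3 as a stand-in for having been treated. That works for a course that runs through day 3. It fails for one that ends sooner, and it fails in both directions: correct treatment of an infected woman becomes a failure, and unneeded treatment of an uninfected woman becomes a success. The second error runs against the trial's stated aim.

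This is a complete rule that gives a wrong answer for an identifiable group, not a detail left open. At stake are dilution of the primary comparison and lost power. If the short courses are concentrated in one network, the exploratory country-by-arm analysis could show a difference produced by scoring. The economic evaluation, which reports cost per unit of appropriate prescribing, could inherit the same error.

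**Working it through.** **The plan's own figure.** Inputs from Sample size calculation: 55% against 70%, α = 0.05, power 0.90, 25% loss. A two-sided two-proportion formula with continuity correction gives 230 per arm, 460 in total, as stated (217 per arm without the correction). 460 / 0.75 = 613.3, rounded up to 614, as stated. The sample size is not in error. Power at 230 per arm without continuity correction is 0.916, the baseline used below.

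**Effect of the rule on an observed rate.** Let π be the share of women with UTI and f the share of treated women whose course ends before day 3. Those women are scored as if untreated: a failure with UTI, a success without. Women who were untreated, or who had an inactive drug for a UTI, keep the same score. In each arm:

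observed rate = (1 − f) × true rate + f × (1 − π)

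With equal f in both arms the last term cancels, so

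observed difference = (1 − f) × true difference.

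A simulation of 2,000,000 women per arm at f = 0.10 agreed: true rates of 55.0% and 70.0% were observed as 54.5% and 68.0%, a difference of 13.5 points.

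**Spain only.** About 154 of 614 women are Spanish, so 154 / 614 ≈ 0.25. If a share s of treated Spanish women finish before day 3, and no one elsewhere does, then f = 0.25s and the trial-wide difference is 15 × (1 − 0.25s). Power is from the two-proportion z-test at 230 per arm; the range covers π from 0.4 to 0.7.

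| s (assumed) | Trial-wide difference, points | Power |
|---|---|---|
| 0 | 15.0 | 0.92 |
| 0.10 | 14.6 | 0.90 |
| 0.25 | 14.1 | 0.87–0.88 |
| 0.50 | 13.1 | 0.82–0.83 |
| 0.75 | 12.2 | 0.75–0.77 |

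The Spanish difference itself shrinks by (1 − s): at s = 0.5 a true 15 points shows as 7.5.

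**How many women are mis-scored.** Illustrative inputs, all assumed: π = 0.5. Controls treat 75% of UTI (85% of those drugs active) and 50% of non-UTI. The POCT arm treats 85% of UTI (95% active) and 30% of non-UTI. s = 0.5.

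- Control: false failures 0.5 × 0.75 × 0.85 × 0.5 = 0.159; false successes 0.5 × 0.5 × 0.5 = 0.125; total 0.284.
- POCT: false failures 0.5 × 0.85 × 0.95 × 0.5 = 0.202; false successes 0.5 × 0.3 × 0.5 = 0.075; total 0.277.

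About 28% of Spanish women are mis-scored, and 0.28 × 0.25 = 7% of the trial. The Spanish rates move from 56.9% against 75.4% (18.5 points) to 53.4% against 62.7% (9.3 points).

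**Unequal shares by arm.** A two-day course started on day 1 covers days 1–2 and misses day 3; started on day 2 it covers day 3. Postponement is described only for the POCT arm, so f could differ by arm. With trial-wide f of 10% in control and 20% in POCT, and π = 0.6:

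- Control: 0.9 × 0.55 + 0.1 × 0.4 = 0.535.
- POCT: 0.8 × 0.70 + 0.2 × 0.4 = 0.640. Difference 10.5 points.
- Shares reversed: 0.520 against 0.670, 15.0 points.
- No true effect (55% in both arms): −1.5 points in the first case, +1.5 in the second.

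These shares only show that the sign can go either way; the protocol gives no basis for a size.

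**The case against.** The strongest reply is that the premise lies outside the document. No regimen is stated, fosfomycin is one of five drugs on one of three plates, and its share of prescriptions is not given. At s = 0 nothing changes, and at s = 0.1 power is still 0.90. Day 3 also has a design logic: it falls after the 24-hour plate result has been acted on. With equal s the error is conservative and leaves type I error intact. The secondary objectives on antibiotic choice, duration and proportion prescribed would still show such treatment. Coding of finished courses might also be left to a fuller document.

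Much of this stands as a limit on size. It does not remove the defect. The rule is stated twice, in full, and its result for a completed course follows from the wording alone. A later document that scored such courses otherwise would be changing the stated primary outcome.

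Two stronger readings are tempting and are not supported. One is that the outcome is wrong for about a quarter of the trial. A quarter is Spain's whole share; the mis-scored share in the illustration is about 7%. The other is that a single dose scores differently by arm because of timing. The protocol does not say that standard-care doses fall on day 1, and the POCT decision comes at about 24 hours, on day 2. A single dose taken then also misses day 3, so it scores the same in both arms. A timing bias needs a two-day course that is postponed, or a dose that slips to day 3.

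**Conclusion.** The point holds as a defect in the scoring rule. Any course completed before day 3 is scored as non-use, which is wrong in opposite directions for women with and without UTI. How often this happens cannot be computed from the protocol. If it is confined to Spain and equal by arm, the planned 15 points becomes 14.6 to 12.2 for s between 0.1 and 0.75, with power between about 0.90 and 0.77 (down to 0.75 at the highest UTI prevalence considered). That fosfomycin is given as a single dose, the value of s, the UTI prevalence and the treatment rates are all assumptions. Fosfomycin's place on a plate of commonly used drugs makes s > 0 plausible, no more.

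With equal s the consequence is attenuation towards no difference. Bias between arms arises only if s differs by arm, and its size and direction are unknown.

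**What to change.** Amend the outcome definition; no treatment changes. Count a woman as an antibiotic user at day 3 if she took an antibiotic on day 3, or had by then completed a course prescribed to end before day 3. Apply this identically in both arms and to both groups: with UTI, then judge susceptibility; without UTI, score as inappropriate. Keep courses stopped early on advice as non-use. If she switched, judge the most recent drug taken by day 3. Report the literal day-3 rule as a sensitivity analysis. Settle this before any outcome data are examined, because the trial is unblinded.

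The cost is a short addition to the definition and some derivation code. Drug, dose and duration are on the baseline CRF for all women, and the diary records antibiotic use over 14 days. There are two downsides. Prescribed duration for later courses is on a CRF only in the POCT arm (the test result form), so later control-arm courses must rest on the diary. And a completed course in a POCT woman without UTI counts against that arm, because by then it can no longer be stopped; the report should say so.

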#### Inclusion criteria

Women aged 18 years and older presenting to primary care with at least one of three key urinary tract symptoms (dysuria, urgency including nocturnal and frequency that have been present for up to 14 days) and where the clinician suspects uncomplicated UTI will be eligible to take part. Patients should be able to provide written informed consent and be willing to complete the patient diary.

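### Women on a current short antibiotic course for another infection are eligible, so that course, not the UTI decision, can set their day-3 score; the effect is slight dilution and misclassification

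*Protocol article*

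**What the plan says.** **Eligibility.** Under Inclusion criteria the article admits "Women aged 18 years and older presenting to primary care with at least one of three key urinary tract symptoms" when the clinician suspects uncomplicated UTI, with no condition on antibiotics being taken for something else. Under Exclusion criteria one item concerns antibiotics. It has two limbs: long-term treatment, and antibiotics received for a UTI in the previous four weeks. The second limb is restricted by indication.

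**Outcome.** Primary objective and Statistical analysis define the outcome by use on day 3. With a UTI, appropriate means "use of an antibiotic for which the isolated pathogen has been shown to have in vitro sensitivity (based on laboratory analysis"). Otherwise: "For women who do not have a UTI, appropriate antibiotic use on day 3 will be defined as no antibiotic use on this day". Neither part asks what the antibiotic was given for. In the UK, UTI status means at least 10^5 cfu/ml of a pure or predominant uropathogen; the article says that definitions in the other countries will be considered.

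**Data.** In the Symptom diary participants "record any antibiotic use over the 14 days". Under Clinical examination the baseline form records "their antibiotic management for the suspected UTI (including name, dose, and duration of any medication prescribed") and other medication prescribed or advised. The notes review covers the three months after recruitment.

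**Purpose.** Statistical analysis justifies testing for clustering at clinician level because "the outcome could be seen as a clinician behavioural measure".

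**The concern.** The outcome is meant to reflect how the suspected UTI was managed. For a woman on a short course for, say, a chest or dental infection, it can reflect something else, in three ways:

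- **No UTI, course still running on day 3.** She is inappropriate by definition, even if the clinician rightly gave nothing for the urinary symptoms.
- **UTI, unrelated drug active against the isolate.** She is appropriate even if nobody chose that drug for the UTI.
- **True UTI, culture suppressed by the drug.** She can fall below the threshold and be classed as having no UTI, so that treating her is scored as an error. The point-of-care plate reads urine from the same visit and is exposed in the same way.

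In the first two cases the score cannot differ by arm, so these women dilute the contrast. In the third, the classification on which the outcome rests is wrong. The cost-effectiveness ratio is expressed per unit improvement in appropriate prescribing, so any dilution carries into it.

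**Working it through.** **Inputs from Sample size calculation:** 55% against 70%, α = 0.05, power 0.90, 230 per arm for analysis, 25% loss, 614 recruited. The sidedness of α is not stated; two-sided is taken because it reproduces the figures.

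**Step 1: reproduce the plan's figure.** With mean proportion 0.625 and difference δ = 0.15:

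n = [1.960·√(2·0.625·0.375) + 1.282·√(0.55·0.45 + 0.70·0.30)]² / 0.15² = 216.8, that is 217 per arm.

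With continuity correction: (n/4)·[1 + √(1 + 4/(nδ))]² = 229.96, that is 230 per arm. This matches. Total 460; 460/0.75 = 613.3, rounded up to 614. The sample size arithmetic is sound and is not in question.

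At 230 per arm the power is 0.900 with the correction and 0.916 without.

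**Step 2: dilution.** Let q be the share of analysed women whose score is fixed by an unrelated course, and s the probability that such a woman is scored appropriate, the same in both arms. The arm rates become (1−q)·0.55 + q·s and (1−q)·0.70 + q·s, so the difference is 15·(1−q) points whatever s is.

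The article gives no value for q. The range of 1% to 5% is assumed; of 460 women it is about 5 to 23.

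**Step 3: power at 230 per arm with s = 0** (all scored inappropriate, the least favourable of the values tried). The corrected column uses the effective size (nδ−1)²/(nδ²), the inverse of the correction in step 1.

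| q | Control | POCT | Difference (points) | Power, corrected | Power, uncorrected |
|---|---|---|---|---|---|
| 0 | 55.00% | 70.00% | 15.00 | 0.900 | 0.916 |
| 1% | 54.45% | 69.30% | 14.85 | 0.892 | 0.909 |
| 2% | 53.90% | 68.60% | 14.70 | 0.884 | 0.902 |
| 3% | 53.35% | 67.90% | 14.55 | 0.875 | 0.894 |
| 5% | 52.25% | 66.50% | 14.25 | 0.857 | 0.878 |

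With s = 0.5 and q = 5%, uncorrected power is 0.885 instead of 0.878, so s matters little.

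**Step 4: can the described data identify these women?** The baseline form covers what is prescribed or advised, not antibiotics already being taken. The notes review starts at recruitment, so a course prescribed earlier lies outside its window. The diary shows that an antibiotic was used; the article does not say that it records why. The eligibility CRF, completed for every consented woman and signed by the clinician, is the one described form on which a check before randomisation fits naturally.

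**The case against.** **The group is small and its size is unknown.** This stands. The course must be current on day 1 and, to fix the score, still running on day 3. Nothing in the article anchors a percentage. At 2% or below, uncorrected power stays at 90% or more. The two-proportion calculation is also only a guide, because the planned analysis is multi-level logistic regression.

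**There is no bias toward one arm.** This stands. A reader might infer that the unrelated courses favour one strategy, but they precede randomisation and should be balanced in expectation.

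**Not every such woman has a fixed score.** This also stands. A reader might infer that neither arm's management can alter any of these scores. The definition does not support that: a woman with a UTI whose unrelated drug is inactive becomes appropriate if the clinician adds an active one. The fixed score applies to women without a UTI who are still on the course, and to women with a UTI whose unrelated drug is active.

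**Existing provisions deal with prior exposure.** Only in part. The two exclusions leave this group in, and the exploratory subgroup by recent antibiotic history does not change how anyone is scored.

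**A fuller protocol or SAP may settle it.** It might add scoring rules. However, the article prints both the exclusion list and the outcome definition, and an analysis plan cannot change who is enrolled or recover a suppressed day-1 culture.

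**Conclusion.** The point holds as a modest design weakness. The printed criteria admit women on a current short course for another infection, and the printed outcome can score them on that course. The consequence is slight dilution and some misclassification of UTI status. Under an assumed 1% to 5%, the difference falls from 15 to between 14.85 and 14.25 points. Power falls from 90% to about 89% to 86% with continuity correction, or from 91.6% to about 91% to 88% without. These figures assume that the affected scores are the same in both arms and, for power, that all are inappropriate. They do not quantify the effect of culture suppression, for which the article gives no basis.

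A reader might also infer that the outcome should count only antibiotics given for the urinary episode. The article does not support that step. The data described do not show what an earlier course was for, and the trial has no blinding, so judging indication could bring in arm-dependent classification where there is now only balanced noise. It could also mark as inappropriate a woman with a UTI who is already covered by an active drug and is given nothing more.

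**What to change.** Add current use of any antibiotic at presentation to the exclusion criteria, and have the clinician confirm it on the existing eligibility CRF before randomisation. This must be in place at enrolment, because a day-1 culture cannot be repeated afterwards.

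Leave the primary outcome scoring rule unchanged.

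Cost: one phrase in the criteria and one check on a form already in use. A few otherwise eligible women are not recruited, and the sample is slightly less pragmatic. The target of 614 does not need to change.
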